## Results

### Gamified Data Curation

A preliminary version of the web interface has been implemented (Figure 4). We are finalizing the features corresponding to video and metadata recording for downstream ML analysis. Over the course of this 5-year study, our objectives are to complete the development of the study’s web system by the end of year 1, begin initial recruitment in year 2, and concurrently conduct human-in-the-loop ML analysis while continuing recruitment from years 3 to 5.

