#### Participant Recruitment and Management

We plan to recruit a total of 400 study participants, comprising 100 individuals formally diagnosed with ADHD, another 100 diagnosed with ASD, a further 100 diagnosed with both ASD and ADHD, and 100 individuals evaluated and confirmed to not have any socially related psychiatric conditions. Our inclusion criteria are as follows: (1) adolescents aged between 14 and 18 (inclusive) years and (2) formally evaluated for ADHD and ASD by a licensed clinician with available documentation. The selection of the final 400 participants that comprise our core data set will be based on the personal information that participants are asked to disclose. Such metadata will be used to ensure a data set that is balanced with respect to race, ethnicity, and gender. The number of participants is based on testing the ability of our system to discriminate between groups of participants. As these groups are balanced, we set the prevalence for binary classification between each condition to 50%. Following a CI of 95%, an estimated theta of 95% [42,48,49], and a width of 15%, the sample size to compute the area under the receiver operating characteristic curve (AUROC) should be 37 [54]. Considering that we have 400 participants, with 100 participants per group, this enables us to follow a common 60:20:20 (train, validation and test ratio respectively) randomized split on the data. That is, we have a sample size (test set) of 40 participants to verify the system’s ability to discriminate between the neurotypical participants and the participants who were diagnosed with either ASD, ADHD, or comorbid ASD and ADHD.

Although formal and well-established methods to perform power calculations for ML analyses have yet to be established, most digital diagnostics studies for conditions such as ASD include <100 participants per class in binary classification [47]. We aim to maintain a similar sample size per diagnostic category. The digital social experiences will be delivered to study participants for 15 minutes each day for a 3-week duration, with a single game out of the 7 possible delivered each day. At least 3 distinct 15-minute sessions will be collected per game for each participant, allowing for comparisons across days for analysis of within-peer consistency.

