#### Evaluation

The diagnostic ML model will be evaluated using balanced classification metrics including AUROC, area under the precision-recall curve, balanced accuracy, precision, recall (sensitivity), *F*_1_-score, and specificity. Performance and CIs will be derived through Monte Carlo cross-validation, with each data split consisting of 300 participants in the training set, 50 participants in the validation set, and 50 participants in the test set. All splits will contain a balance with respect to the 5 diagnostic classes, age, gender, race, and ethnicity.

To evaluate the effectiveness of the active learning querying system, we will run post hoc simulations comparing the random selection of new data against targeted requests using active learning. We will train the classification system with 12 sessions of data, hold out the remaining 9 sessions, and plot the performance of each metric against the number of additional samples acquired using both active learning and random selection of data segments.

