When verifying the automatically extracted computational features manually, it is possible that some features will be incorrect. Computational feature extraction approaches are not perfect and are not necessarily robust to unforeseen conditions (eg, dim lighting, obfuscation of certain body parts, and unfamiliar accents). If any feature is consistently unreliable across several participants, then we will remove that feature from the study. There are sufficient features available, so if some do not function as intended, the study can still proceed.

It is possible that the large number of features used to train the DL classification models will be overfitted to the training set, as a data set of 400 samples (of which approximately 300/400, 75% would be in the training set) is relatively small for ML and is unlikely to capture all the intricacies of social behavior that can be expressed with the feature space. If this happens, we will run feature selection and dimensionality reduction algorithms to reduce the number of features used in the model to a minimum viable set and to summarize the feature space in a low-dimensional manner, respectively. The feature selection will enable interrogations into which features are most useful in the differentiation of each condition.

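### Reported AUROC may be optimistic: cross-validation uses all 400 participants, and the results-triggered feature reduction is not confined to each split's training data

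*Protocol article*

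**What the plan says.** Four places in the protocol article bear on this.

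- **Methods, Multicondition Diagnostics, Evaluation:** "Performance and CIs will be derived through Monte Carlo cross-validation". The split sizes are fixed in the same place and add to the full sample: "with each data split consisting of 300 participants in the training set, 50 participants in the validation set, and 50 participants in the test set".
- **Discussion, Limitations:** overfitting is foreseen for a data set of 400 with about three quarters in training, which is the same split. The response is "If this happens, we will run feature selection and dimensionality reduction algorithms to reduce the number of features used in the model". The selection is also meant to show "which features are most useful in the differentiation of each condition".
- **Results, Gamified Data Curation:** the timeline says the team will "concurrently conduct human-in-the-loop ML analysis while continuing recruitment from years 3 to 5".
- **Methods, Participant Recruitment and Management:** "We plan to recruit a total of 400 study participants", 100 per diagnostic group. The sample-size argument there uses a different scheme: "this enables us to follow a common 60:20:20 (train, validation and test ratio respectively) randomized split on the data", and "we have a sample size (test set) of 40 participants".

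Other model choices are left open in Methods: a recurrent network or an attention-based model, separate or multitask classifiers, and mean crowd ratings or a fitted model for each behaviour.

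**The concern.** Cross-validation gives an honest performance estimate only if every step that used the diagnostic labels is repeated without the test participants. A feature reduction judged on how well features separate the conditions uses the labels. The fallback reads most naturally as one revision of the model for the whole study, made after overfitting has been seen in the planned splits. On that reading, the participants whose labels shaped the reduced model come back as test participants when the splits are redrawn.

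The validation part of each split does not prevent this by itself, because one split's validation participants are another split's test participants. Analysis alongside recruitment adds a second occasion on which early participants could influence the design.

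Classification performance is the study's main result. The bias would shift the point estimate, so a correctly computed interval would be centred on too high a value.

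**Working it through.** **1. The plan's own figure.** Inputs from Participant Recruitment and Management: AUROC A = 0.95, 95% CI of total width 0.15, prevalence 50%. The Hanley-McNeil variance is

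[A(1−A) + (n1−1)(A/(2−A) − A²) + (n2−1)(2A²/(1+A) − A²)] / (n1·n2).

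With n1 = n2 = 18.5: 0.0475 + 17.5 × (0.00226 + 0.02314) = 0.492. Divided by 342.25 this is 0.001438, so SE = 0.0379 and the width is 2 × 1.96 × 0.0379 = 0.149. Solving for a width of exactly 0.15 gives N = 36.4, rounded up to 37. The stated 37 reproduces.

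**2. Who is left out of the resampling.** 300 + 50 + 50 = 400, so nobody. The other scheme gives 240/80/80 of 400. Its test set of 40 is 20% of the 200 people in a two-group contrast. The two schemes are not the same plan.

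**3. Overlap, if m people had guided a study-level choice.** The chance that a random test set of 50 contains none of them is C(400−m, 50)/C(400, 50), and the expected number included is 50m/400. The article does not give m, so a range is shown.

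| m | P(none in test set) | Expected in test set |
|---|---|---|
| 20 | 0.065 | 2.5 |
| 50 | 0.0008 | 6.25 |
| 100 | 2 × 10⁻⁷ | 12.5 |
| 200 | 3 × 10⁻¹⁷ | 25 |

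From about 50 people upward, practically every test set would include some.

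**4. Possible size.** Simulation: 200 v 200 participants, the 20 features most associated with the label, a linear classifier, 20 splits of the 300/50/50 type, 60 data sets per setting. Selection was made once on the first 100, 200 or all 400 participants, or repeated inside each training set (nested). Fresh-data AUROC comes from 2,000 new people, averaged over 40 separate data sets. Feature counts, selector, classifier, signal and interim sizes are my assumptions. Triplets are for selection on the first 100 / 200 / 400; the third decimal is not reliable.

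| Features | True signal | Cross-validated | Fresh data | Excess | Nested |
|---|---|---|---|---|---|
| 100 | none | 0.551 / 0.590 / 0.650 | 0.497 / 0.501 / 0.501 | 0.054 / 0.089 / 0.149 | 0.505 |
| 100 | 10 at 0.3 SD | 0.692 / 0.732 / 0.764 | 0.649 / 0.678 / 0.686 | 0.043 / 0.054 / 0.078 | 0.683 |
| 100 | 10 at 0.6 SD | 0.899 / 0.909 / 0.914 | 0.887 / 0.891 / 0.894 | 0.012 / 0.018 / 0.020 | 0.892 |
| 500 | none | 0.590 / 0.651 / 0.737 | 0.503 / 0.497 / 0.501 | 0.087 / 0.154 / 0.236 | 0.501 |
| 500 | 10 at 0.3 SD | 0.669 / 0.732 / 0.794 | 0.585 / 0.616 / 0.658 | 0.084 / 0.116 / 0.136 | 0.631 |
| 500 | 10 at 0.6 SD | 0.882 / 0.911 / 0.923 | 0.846 / 0.883 / 0.881 | 0.036 / 0.028 / 0.042 | 0.878 |

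Nested selection shows no upward bias. Against fresh data with selection on 400, it differs by between −0.027 and +0.004. The lower values are expected, since it selects on 300.

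A second simulation with a ridge classifier agrees. With no signal and selection on the first 200, AUROC was 0.56, 0.61 and 0.66 for 60, 200 and 1,000 features, against a truth of 0.50.

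**The case against.** A reader might infer that the plan revises models during recruitment, that every test set therefore contains people used to choose the model, and that reported performance is inflated. The documents do not support this.

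- The timeline sentence does not mention interim performance, label use or revision. Elsewhere in the article the human-in-the-loop part is crowd tagging of behaviours, so tagging and extracting features as videos arrive would satisfy it.
- The feature reduction is a conditional fallback in Limitations, with no stated timing. It speaks of overfitting to the training set, so selection inside each split is compatible with the text. Dimensionality reduction need not use labels at all.
- The simulated excess presupposes selection done once outside the splits. The preliminary results (AUROC 0.815 for audio, above 0.95 for crowd ratings, both for autism alone) suggest real signal, where the excess is smaller.
- How selection is nested is a detail that an article may leave to a fuller document.

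The first three points stand and limit the wording to a risk. The last stands only in part. The article does fix a resampling scheme that uses all 400 people and a results-triggered reduction of the model. Following both in their natural reading scores people whose labels helped to choose the features. A fuller document that held participants out of the resampling would contradict the stated split sizes.

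**Conclusion.** The concern holds as a risk: reported AUROC may be optimistic, because no participant is protected from model development and the fallback is not tied to the training data of each split. It becomes a bias only if feature reduction or model choice is made at study level after results are seen.

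The size cannot be derived from the article. Under the assumed settings the excess is about 0.01 to 0.04 with strong signal (fresh-data AUROC 0.85 to 0.89), about 0.04 to 0.14 with weak signal, about 0.05 to 0.24 with none, and absent when selection is nested. The article itself expects accuracy to fall once ADHD is added, so the strong-signal case cannot be taken for granted.

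Separately and without assumptions, the 300/50/50 and 60:20:20 schemes conflict. The 60:20:20 split would not cure the problem unless it were drawn and locked before the concurrent analysis starts.

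**What to change.** 1. In Evaluation and Limitations, state that any label-based feature selection, dimensionality reduction, tuning, calibration and model choice is repeated using only the training and validation parts of each split. State that the overfitting trigger is never judged on test-part results. Because validation participants rotate into other test sets, apply the trigger as a rule within each split and not once across splits. This costs wording and computing time, with no extra participants.
2. Reconcile the 300/50/50 cross-validation with the 60:20:20 split and its test set of 40, and say which one yields the reported result.
3. Optional: if the 20% test set is kept, draw 20 per diagnostic group (80 in all), lock it before the concurrent analysis starts, and report the frozen model on it. A two-group contrast then has 40 people. At an AUROC of 0.95 the CI width is 0.143, inside the planned 0.15. The price is 320 instead of 400 participants for development, and a less precise estimate from a single test set.

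The choice should be made before the year 3 analysis, because participants whose labels have guided design cannot be made untouched again.

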**Figure 4 figure4:**
[figure not shown]
Preliminary interface for the study’s central web platform. (A) Users who are not a part of the core user study where participant matchmaking occurs can select their game play partner. (B) One of the implemented games, Charades.

### Novel Crowd-Powered and Traditional ML-Based Feature Extraction

We have conducted a series of preliminary studies testing the use of crowdsourcing for precision behavioral health, demonstrating that although there is a high degree of variability in crowd workers’ innate ability to rate complex social behaviors in unstructured home videos [10], there exists a small fraction of crowd workers on platforms such as Amazon Mechanical Turk who consistently rate in alignment with licensed clinical experts [48,49]. In a study, we demonstrated that a group of 40 crowd workers filtered from an original pool of >1000 workers was able to rate behaviors that, when fed into a classifier trained on clinician records, achieved an AUROC of 0.9904 for one set of features and 0.9872 for another feature set [42]. Our experience of receiving approval from university IRBs and data privacy offices as well as obtaining consent from families to share their videos with crowd workers mitigates any risks related to this novel process.

After applying privacy-preserving modifications to the videos, such as pitch shifting the audio downward and using face detection to box out the child’s face, the performance of the model remained >0.95 for both AUROC and area under the precision-recall curve [42]. Although these results show promise for predicting autism in a binary task, they are likely to decline in accuracy when expanding to include ADHD as a diagnosis too. These studies provide strong evidence to support the proposed worker matching procedure, which will enable the more nuanced feature space required for multicondition classification. The prior experience in developing automated pipelines for managing crowd workers will help streamline the development of the crowd management scripts.

The feasibility of the automatic feature extraction steps comes from the existing packaging of the required functionalities into Python libraries and the high documented performance of these tools. All the ML-powered feature extractors we have used are well documented.

### Multicondition Diagnostics With Adaptive Input Querying

In 1 of our preliminary experiments involving 4-way ASD or ADHD classification (only ASD vs only ADHD vs both vs none) using publicly available survey data, a decision tree classifier achieved an *F*_1_-score of 0.75 and Hamming loss of 0.23. The final data set consisted of 270,978 data points and 60 columns, with which we attempted multiple feature selection methods such as recursive feature elimination, decision tree feature importance scores, and logistic regression coefficients to quantify the strength of the relationship between the predictor variables and target variables. Across all 3 methods, the highlighted behavioral features were difficulty in making or keeping friends; difficulty in dressing or bathing; having behavioral problems; having difficulty concentrating, remembering, or making decisions; having anxiety; arguing too much; and sharing ideas or talking about things that really matter. On the basis of these observations, we believe that the games targeting behavioral and motor skills, mentioned in Table 2, can support the research findings and generate relevant data. We will modify the currently implemented games to specifically target these newly identified behavioral features.

The feasibility of DL models relies on the underlying data used to train them. DL has the capacity to learn any discriminative function, provided it has a large enough model and adequate computational power to train a large model. University of Hawai‘i at Mānoa has provided us with a dedicated Nvidia v100 graphics processing unit node and a dedicated Nvidia RTX5000 [61] for computationally intensive research. In addition, the Hawai‘i Data Science Institute has shared computing resources consisting of 346 nodes (8500 cores) with 63.19 terabyte of RAM, 120 graphics processing units, and >1 petabyte of storage. These resources are free to use for University of Hawai‘i laboratories. Collectively, these resources are more than sufficient to train DL models for the proposed data set size.

We have previously trained DL models for making a binary prediction of ASD (Table 3).

**Table 3 table3:** Preliminary data supporting the use of multimedia data from social games to predict autism spectrum disorder.

Data modality	Prediction performance
Audio	AUROC^a^: 0.815 (0.077 or −0.077)
Facial emotion	Balanced accuracy: 71%
Eye gaze	Recall: 66.2%; precision: 63.5%

^a^AUROC: area under the receiver operating characteristic curve.

Although each of these models used a single data modality (audio, facial emotion expression, or eye gaze), their performances were on par with prior literature [47]. We hypothesize that incorporating additional modalities will not only allow for increased performance within a single class but will also enhance discriminative power across diagnostic categories.

## Discussion

### Principal Findings

There is a great need for improved, scalable, and accessible diagnostic assessments for neuropsychiatric conditions that require accurate and extensive evaluations. We propose to use a multimodal ML model to study heterogeneous psychiatric conditions through human-in-the-loop computing. Although DL models have been able to successfully classify participants with ASD from their neurotypical peers in prior work, the human-in-the-loop observations can help extract a more nuanced feature subset for the diagnosis of similar yet distinct conditions. We have deployed an initial set of games on the web interface targeting behavioral features, and we have extracted a subset of core behavioral features that aligns with the proposed games and can thus help us to effectively target our digital diagnostic. The crowd worker ratings appear to be of high quality based on our prior studies, aligning with the computationally extracted features and clinician’s records, even after the videos are modified. Moreover, the reduced feature subset extracted using preliminary studies from multiclass classification of publicly available survey data has helped us identify the core behavioral features that we intend to target through our gamified approach.

This study aligns with multiple previous works [1,2,5-11,15-41] where the researchers worked with single-modality data to capture the phenotypic behaviors of ASD, ADHD or both. These studies were not only limited by the availability of social features but also by the small size and lack of diversity in the data set [1]. By contrast, our study encompasses several sources of information such as facial emotion, body movements, audio streams, and crowd worker ratings that will improve the predictive capability of the model for comorbid diagnosis and capture the overlapping features. Through this study, we aim to bridge the gap posed by diagnostic and therapeutic challenges in psychiatry using ML techniques. Such noninvasive studies can better use the complex social behaviors to characterize behaviors specific to ASD and ADHD.

The technical aspects of the project are highly feasible, with modest development requirements compared with modern real-time computer gaming systems. The web server will be developed using the Django Python framework [62] and hosted on an Elastic Compute Cloud (EC2) instance [63] on AWS, with extensive existing functionality and documentation existing for all technologies used. Extensive codes are available on the internet for implementing the video and audio chat features. A full-time developer, an engineering or computer science student, or a postdoctoral researcher can implement the entire system within the span of 4 person-months.

### Limitations

Although our initial findings are optimistic, there are some limitations to the study. The primary challenge will be the recruitment and retention of 400 study participants, including the formal clinical validation of the diagnosis for each participant. Although this study can be successfully completed with fewer participants, smaller data sets can affect the model’s learning capability, leading to overfitting, noisy outliers, or sample bias. To help manage this recruitment effort, we will hire a full-time clinical research coordinator to recruit and manage the participants. We will work with the clinical collaborators in the Department of Psychiatry to recruit in Hawaiʻi’s psychiatric clinics, where our collaborators and their colleagues practice. This will be supplemented with web-based recruitment using targeted advertisements on social media. We have discussed this recruitment plan and desired study size with our collaborators in the Department of Psychiatry, and we hold recurring monthly meetings to strategize about participant recruitment using both our existing access to several clinics in Hawaiʻi and web-based targeted recruitment. In addition, our former mentor and collaborator, [name] at Stanford University, has access to hundreds of families with adolescent children diagnosed with ASD as well as comorbid ADHD. He is the founder of Cognoa [53,64-69], an artificial intelligence–based digital diagnostic tool for studying early childhood development and pediatric behavior.

There might be technical challenges associated with web applications or user interfaces, which may occur at later stages of the study. The proposed data curation game platform may lack qualities that would garner repeated participant engagement over a 3-week period, such as poor user interface design, poor design of the automated notification system, or poor entertainment quality of the individual games. To mitigate this risk, we will run several iterative design sessions regarding proper implementation of the design process to maximize both user engagement and high-fidelity data collection. We will run several pilot studies to obtain both qualitative and quantitative measures of engagement before running the primary data collection study.

The other potential pitfalls are compliance and tardiness. We will run automated computer vision checks in real time to ensure participant compliance with camera calibration requirements. Another script will send automated text messages and email reminders to late participants, assigning them to makeup sessions. If these mitigation steps fail or if recruitment is unsuccessful and there are <100 participants with valid data per diagnostic category, the study can still be successful with as few as 20 participants per class, as ML studies with approximately 20 participants per diagnostic category have frequently been published in the field [47].

There are also limitations associated with crowdsourcing based on the expertise of the crowd workers or their temporal availability. Although this never occurred during preliminary data collection, a potential pitfall is that some questions may have no workers who consistently rate them in accordance with clinicians. If this occurs, then that question will be removed from any further components of the study (ie, removed as a feature for the diagnostic classifier).

In crowdsourcing, scaling the number of workers does not correlate with the time spent on recruitment. However, to ensure high-quality annotations, we do anticipate spending a considerable amount of time recruiting crowd workers. As mentioned previously, we plan a crowd worker profiling phase based on 20 tasks and data collected through pilot studies with our data-gathering platform. By periodically posing a gold-annotated question and providing a monetary bonus for correctly answering such questions, we incentivize workers to provide high-quality answers. On the basis of our prior studies, we expect that the level of compensation will lead to a worker retention rate of >90%. Furthermore, to account for the loss of workers, we will recruit 3 times more crowd workers than is minimally required for the study. With regard to the number of crowd workers required, we follow the study by Roitero et al [70]. As such, the recommended number of workers will be estimated based on a small amount of data collected during our pilot studies.

When verifying the automatically extracted computational features manually, it is possible that some features will be incorrect. Computational feature extraction approaches are not perfect and are not necessarily robust to unforeseen conditions (eg, dim lighting, obfuscation of certain body parts, and unfamiliar accents). If any feature is consistently unreliable across several participants, then we will remove that feature from the study. There are sufficient features available, so if some do not function as intended, the study can still proceed.

It is possible that the large number of features used to train the DL classification models will be overfitted to the training set, as a data set of 400 samples (of which approximately 300/400, 75% would be in the training set) is relatively small for ML and is unlikely to capture all the intricacies of social behavior that can be expressed with the feature space. If this happens, we will run feature selection and dimensionality reduction algorithms to reduce the number of features used in the model to a minimum viable set and to summarize the feature space in a low-dimensional manner, respectively. The feature selection will enable interrogations into which features are most useful in the differentiation of each condition.

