### Novel Crowd-Powered and Traditional ML-Based Feature Extraction

#### Description

We will create 2 pipelines for converting raw video and audio data into interpretable feature vectors that quantify social behavior relevant to ADHD and ASD diagnostics. For behaviors that can be feasibly quantified using computational methods, we will use existing toolkits. For highly complex and nuanced social behaviors that are beyond the scope of current ML tools but that are highly relevant to psychiatric classification, we will use a novel crowdsourcing pipeline to match crowd workers to labeling tasks.

We will perform automatic feature extraction for behaviors potentially related to diagnoses such as the percentage of total conversation time contributed by the participant, eye gaze patterns during the gameplay including the proportion of gaze directed toward the game versus the live video feed of the other participant, vocal prosody and intonation during conversation, natural language processing analysis of the content of the conversation after converting raw audio to text using speech-to-text programs, and breaks in task flow as measured by pauses in game-related keystrokes and mouse movements. The extracted information will be stored for each frame at a sampling rate of 5 frames per second. As depicted in Figure 2, each of these features will be concatenated into a temporal feature vector and used to train a time series DL model such as a long short-term memory recurrent neural network or an attention-based model (eg, transformers). There are existing Python libraries that enable the proposed automatic behavioral feature extraction such as OpenFace [56] and MediaPipe for eye gazing. For facial emotion recognition, we will use Amazon Rekognition [57], an AWS service that provides recognition of disgust, happiness, surprise, anger, confusion, calmness, and sadness in addition to other relevant facial features such as whether the eyes and mouth are open. In the audio domain, pitch will be extracted using the Convolutional Representation for Pitch Estimation library [58], and waveforms will be processed using the librosa library [59].

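### Recruitment source is liable to be confounded with the ASD label, because one source is named only for ASD families and source is not among the balanced variables

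*Protocol article*

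**What the plan says.** **Sources (Discussion, Limitations).** Recruitment is planned in Hawaiʻi's "psychiatric clinics, where our collaborators and their colleagues practice". The section adds: "This will be supplemented with web-based recruitment using targeted advertisements on social media". It then mentions, as a further resource, a collaborator at another university who "has access to hundreds of families with adolescent children diagnosed with ASD as well as comorbid ADHD". No number or share is given for any source. The network is not mentioned for ADHD-only participants or for those with neither condition.

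**Groups (Methods, Participant Recruitment and Management).** "We plan to recruit a total of 400 study participants, comprising 100 individuals formally diagnosed with ADHD", with 100 each for ASD, for both conditions and for neither. Every participant must have a documented formal evaluation for ADHD and ASD by a licensed clinician.

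**Balancing.** At selection (same section): "Such metadata will be used to ensure a data set that is balanced with respect to race, ethnicity, and gender". In the splits (Multicondition Diagnostics With Adaptive Input Querying, Evaluation): "All splits will contain a balance with respect to the 5 diagnostic classes, age, gender, race, and ethnicity". The count of five classes there, against four groups elsewhere, is a separate matter. Neither list contains recruitment source, site or location.

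**Inputs (Feature Extraction, Description).** The model uses gaze, facial and vocal features, including prosody, and "natural language processing analysis of the content of the conversation after converting raw audio to text using speech-to-text programs". The Limitations section accepts that automatic extraction may not be robust to conditions such as "dim lighting, obfuscation of certain body parts, and unfamiliar accents".

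**The concern.** A classifier trained on home recordings can use anything in them that tracks the label. Families from one clinical network may differ from families reached through clinics or advertisements in speech, home setting, equipment or familiarity with research. If one source supplies mainly ASD-positive participants, those differences predict ASD without being behavioural signs of it.

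The planned evaluation would not show this. Monte Carlo cross-validation draws training, validation and test sets from one pool, so a link between source and diagnosis is expected to be equally strong in all of them and would count as correct prediction. Removing unreliable features does not help, because a source cue can be measured reliably. Feature selection would tend to keep a cue that predicts the label. The article describes no source-only benchmark and no analysis that holds a source out.

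At stake is the study's central claim that the model recognises behaviour. An ASD AUROC raised by source would not carry over to a setting where all referrals arrive by one route.

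**Working it through.** **The plan's own figure.** The only calculated size is 37 participants, for an AUROC of 0.95, a 95% interval of width 0.15 and 50% prevalence. The Hanley-McNeil standard error with equal classes and 0.15 as the full width gives 37, so the figure reproduces. It matters here only because it sets 0.95 as the expected AUROC. The article gives no figure for source.

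**Inputs.**
- From Participant Recruitment and Management: four groups of 100, hence 200 ASD-positive (ASD-only and both) and 200 ASD-negative (ADHD-only and neither).
- Assumed, because not stated: s, the share of ASD-positive participants who come from the network, and u, the same share among ASD-negative participants.
- Assumed: the model can read network membership fully from the recordings. This makes the results upper bounds for a source-only shortcut.

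**ASD label.** A rule that calls network participants ASD-positive has sensitivity s and specificity 1 − u. For a binary marker,

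AUROC = (sensitivity + specificity)/2 = (s + 1 − u)/2 = 0.5 + (s − u)/2.

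| s | ASD-positive participants from the network | AUROC, u = 0 | AUROC, u = 0.10 |
|---|---|---|---|
| 10% | 20 of 200 | 0.55 | 0.50 |
| 25% | 50 of 200 | 0.625 | 0.575 |
| 50% | 100 of 200 | 0.75 | 0.70 |
| 75% | 150 of 200 | 0.875 | 0.825 |
| 90% | 180 of 200 | 0.95 | 0.90 |

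When s = u, the AUROC is 0.50: equal source mixes remove this shortcut.

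**ADHD label.** ADHD-positive participants are the ADHD-only and comorbid groups; ADHD-negative participants are the ASD-only group and those with neither. If a share s of both ASD-only and comorbid participants comes from the network and nobody else does, the network share is s/2 among ADHD-positive and s/2 among ADHD-negative participants. The AUROC is 0.5 + (s/2 − s/2)/2 = 0.50.

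**Four-way outcome.** Under the same assumption, the best source-only rule names one ASD group inside the network (100s correct) and one non-ASD group outside it (100 correct). Accuracy is (100s + 100)/400: 0.25 at s = 0, 0.375 at s = 50% and 0.50 at s = 100%.

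**Effect of balancing the splits.** Balancing the splits on source would only make s and u equal between training and test sets. It would leave s − u unchanged, so the bias would remain. The balance that matters is across diagnostic groups when the 400 are selected.

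**The case against.** The strongest objection is that the article does not commit to enrolling anyone from the network. The main routes are clinics and web-based advertisements, and the network is mentioned as additional access in support of feasibility. Both main routes can supply ASD and comorbid participants, so s could be small, and at s = 10% even the upper bound is only 0.55. This stands. The point is a risk built into the plan, not an established bias.

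A reader might infer more than the document supports:

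- **That source is confounded with diagnosis as a matter of fact.** No share is stated, so this cannot be known.
- **That controls must come mostly from advertisements.** Controls need a formal evaluation too, so adolescents assessed and found to have neither condition could come from clinics. The asymmetry of the network does not depend on this.
- **That the network families live outside Hawaiʻi.** Only the collaborator's university is given. Differences in accent or location are therefore possible, not documented.
- **That the whole model could score well from source.** With equal draws from the two ASD groups, only the ASD label is exposed.

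There are partial safeguards. Camera zoom and body position are calibrated before each session, race and ethnicity are balanced, and crowd-tagged behaviours carry source less directly than raw audio. None of these removes differences in voice, speech content or setting.

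It can also be said that a condensed article need not describe source logging or quotas. That is fair for operational detail. But the article states its balancing variables twice and names a diagnosis-specific source, and the point concerns those statements together.

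**Conclusion.** The concern holds as a liability. The article names one source for the two ASD groups only, leaves source out of both balancing lists, and plans an evaluation that cannot tell a source signature from behaviour. The size is unknown. Under full recoverability and u = 0, the upper bound on ASD AUROC from source alone runs from 0.55 at s = 10% to 0.95 at s = 90%; the last equals the AUROC that the sample size assumes. Any network recruitment of ASD-negative participants lowers these figures, and incomplete recoverability lowers the shortcut's contribution further. The ADHD label stays at 0.50 if the ASD-only and comorbid groups draw equally on the network.

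The change is worth making before recruitment, which the Results section places in year 2, because a source that supplies only one class cannot be adjusted for afterwards.

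**What to change.** 1. Record recruitment source for every participant.
2. Add source to the selection variables in Participant Recruitment and Management, so that, as far as the available pool allows, the final 400 have similar source mixes across the four groups.
3. Report the AUROC of a model given source alone, as a benchmark beside the ASD AUROC.
4. Report ASD performance with network participants excluded from both training and testing, and within each source that contains both ASD-positive and ASD-negative participants.
5. If a source supplies only one class, say that ASD performance cannot be separated from source for those participants. AUROC within such a source is undefined.

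The cost is one extra field, some extra analysis, wider intervals in the restricted analyses and possibly a lower reported AUROC. For example, at s = 50% and u = 0, excluding the network leaves 100 ASD-positive and 200 ASD-negative participants, 300 of the 400. Recruitment quotas matched by area are optional and not part of this fix: they would burden recruitment, which the article already calls its main challenge.
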